## Protocol

This is version 2 of the protocol from the 22
^nd^ of December 2020.

### Study setting

The study will be conducted at a reference tertiary cancer hospital that will be selected based on willingness to participate and availability of qualified participants willing to take part in the study.

### Randomization

We plan to conduct a single hospital trial and randomization will be done by the OxMaR software. Allocation sequence will be concealed for everyone involved in the trial, except for the pharmacist and the nurse responsible for patient’s allocation. This allocation will remain hidden for health care professionals and participants until the final result of the study are obtained
^20^.

First approach will be performed by patient's physician and subsequent recruitment steps will be conducted by trained clinical staff. Written informed consent will be explained and signed. The recruiting physician will have access to a computer with OxMar software, the initial forms will be fulfilled and imputed personal data should be confirmed. The software will generate the allocation, which is automatically sent to the pharmacist that will provide the medication or placebo to the participant. The access to this allocation will be protected by Swordfish (
http://www.swordfishsecurity.com/).

The pharmacist will be responsible for formulating and packaging (identically) the trial medicines (placebo and esketamine nasal spray). He or she will label and deliver them with corresponding randomized number received from OxMar records.

### Blinding

All investigators, patients, care providers, outcome assessors, and study statisticians will remain blinded with respect to the treatment allocation throughout the trial. The masking will be assured by delivering identical unlabeled nasal injectors with the same volume (200 μL) and color of active drug and placebo. Each device will deliver 28mg of esketamine or placebo in a 200 μL solution, so in order to achieve the 56mg dose two devices will be required
^21,
22^.

Esketamine nasal spray has a certain taste often described as bitter, that can cause dysgeusia. Therefore, blinding of subjects will be further guaranteed by adding denatonium benzoate to the water-based placebo agent mimicking the taste of esketamine intranasal solution.

On each dosing day during the trial, participants will self-administer at 2 time points 1 spray of the study drug (esketamine or placebo) into each nostril. Each administration will be separated by 5 minutes. The administration will take place at the facility to ensure adherence and surveillance in regard to side effects.

***Emergency unblinding.*** In case of problems and safety concerns that cannot be solved with on-going blinded treatment, the participant’s allocated intervention will be revealed. Unblinding procedure will be performed at the request of the Data Monitoring Committee (DMC; see information below).

During the period of treatment, the patient's status will be evaluated weekly by an experienced blinded anesthesiologist. Vital signs and oxygen saturation levels will be examined and recorded. Also a physical examination will take place to follow up the patients’ functional status.

Sealed envelopes will be stored safely and access will be available 24/7 if needed. Treating physicians and the responsible pharmaceutical staff will be instructed and encouraged to maintain blinding status if possible. Certainly, they are advised to maintain blinding towards other subjects and ensure disclosure towards corporate sponsors, office staff, data analysts and study personnel.

The Investigator must report all code breaks (with reason) as they occur on the corresponding electronic case report form page. Unblinding should not necessarily be a reason for study drug discontinuation.

### Eligibility criteria

*Inclusion criteria*:

Age ≥ 18 years; Male or female patients.Patients with refractory cancer pain, defined as: multiple evidence-based biomedical therapies used in a clinically appropriate and acceptable fashion have failed to reach treatment goals that mainly include adequate pain reduction and/or improvement in daily living functioning activities; AND/OR patients’ functional activities do not allow a quality of life, which is acceptable and/or pharmaceutical therapies have resulted in intolerable adverse effects.Psychiatric disorders and psychosocial factors that could influence pain outcomes have been assessed and appropriately addressed
^23,
24^; in practice, when the patient with cancer pain responds positively to any of these two questions:1.Is your pain under the current drug medication intolerable for your quality of life?2.Do you have intolerable adverse effects with your current treatment?Cancer pain classified as chronic (persistent or recurrent pain lasting longer than 3 months)
^25^, and currently refractory despite optimized analgesic therapy including an opioid. [Optimized analgesic therapy is arbitrarily defined as: oral morphine equivalent of 60 mg/d or more
^11,
26^ (or another strong opioid at optimized dose) plus at least one adjuvant analgesic drug, for at least 2 weeks.]No increase in baseline long acting opioid dose or addition of a new adjuvant analgesic drug within 2 weeks prior to study entryAbility to communicate the intensity of pain using the NPRS pain scale ranging from (0 as no pain to 10 with severe pain).Ability to give fully informed written consent.Expect survival more than 3 months.

*Exclusion criteria*, taking into consideration the safety profile of the drug
^22^ were defined as:

History of allergy or intolerance to esketamine or ketamine.History of allergy to disinfecting products containing quaternary ammonium, who might be susceptible to be allergic to denatonium benzoate.Concomitant use of xanthine derivatives (e.g. aminophylline, theophylline), ergometrine, or monoamine oxidase inhibitors.Active nasal/sinus dysfunction (e.g. allergic or infectious rhinitis) or presence of any lesion of the nasal mucosa.Pregnancy, breastfeeding and women of childbearing potential not using a highly effective contraception method.Uncontrolled hypertension, arrhythmia, heart failure, or untreated coronary artery disease. History of transient ischemic attacks, stroke, neurovascular disease, hemorrhage, severe head injury, hydrocephalus or elevated intracranial pressure within the last 3 months.History of primary or metastatic malignant brain lesions (uncontrolled or without previous treatment).Known aneurysmal vascular disease (including thoracic and abdominal aorta, intracranial, and peripheral arterial vessels) or arteriovenous malformationUncontrolled psychiatric illness with psychosis/hallucination (e.g. schizophrenia, acute psychosis).Alcohol abuse, drug abuse/dependence within the past 6 months as self-reported.Cirrhosis or severe hepatic impairment defined as 5-fold elevation of transaminases.Uncontrolled hyperthyroidism.Globe injuries or increased intraocular pressure (e.g. glaucoma).History of ulcerative or interstitial cystitis.Subjects scheduled to receive radiotherapy (RT) to a site of pain during the study period, or who have received RT to a site of pain within 2 weeks before study entry.Subjects scheduled to undergo surgical treatment during the study period likely to affect pain.Subjects on or starting chemotherapy if there is a significant expectation of that therapy affecting pain.Subjects who have not provided signed informed consent form.Concomitant use of drugs moderately or severely affecting cytochrome P450 activity.

### Recruitment strategy

Participants will be recruited at the oncology and pain clinics of a tertiary academic hospital by the attending physicians during routine appointments. Participants may also be identified via review of medical records from the oncology and pain clinics and contacted by telephone prior to the next scheduled appointment with information about the study, in order to allow more time for consideration. Screening will continue until the target sample size is achieved (120 subjects as calculated sample size, see below). Expected recruitment time will be two years.

### Adherence

To achieve adherence in the present clinical trial, the characteristics and main objective of the study will be exposed to the patients and their relatives who are in charge of their care during recruitment interviews and informed consent. An instructional video will be provided, which contains information about the correct drug administration, as well as the benefits of having a quick and easy application therapy. Adjuvant drugs currently used will be provided at each visit.

In the initial interview with the subject the following information will be given:

-Objectives of the study-Mode of administration of interventions-Importance of continuing with regular treatment (opioids, antidepressants, etc.)

### Timeline

Figure 1 demonstrates a timeline with concise description of scheduled visits and assessments.

**Figure 1. f1:**
[figure not shown]
Timeline of scheduled visits and assessments. This figure displays the scheduled timeline of the study. Included are randomization, application of study drug/placebo (nasal spray devices), clinical assessments and time point of data collection (results).

### Interventions

The patients will be using around the clock baseline analgesia with long-acting opioid, and morphine rescue dose for the management of breakthrough pain. In the case of neuropathic pain, patients should start the use of an antidepressant or anticonvulsant in an optimized dose. If the participant is already using any of these drugs, they should continue the medication
^1^ .

The study drug will be provided in two disposable nasal spray devices containing either 28 mg of esketamine or placebo in a 200 uL of solution - equivalent to two sprays doses. The 28 mg esketamine nasal spray device labeled “Spravato
^TM^” and a similar placebo device should be provided by the manufacturer Janssen Pharmaceutical Company of Johnson & Johnson. The participants should initially self-administer the nasal spray device containing either active drug or placebo under the supervision of a health care provider in the researcher center. Health care providers (physicians or nurses) will be informed and trained prior to the beginning of recruitment. Training will be provided by the investigators. One spray must be administered into each nostril in a 45-degree reclination to deliver 28mg. After a 5 minute interval the second device is used to deliver the second 28mg dose or placebo
^22^.

The nasal spray device contains an indicator with two green dots referring to the two spray doses. After one spray is delivered, one green dot will disappear. When the device empties after the two doses, all green dots will have disappeared. The participants will receive the intervention twice weekly for 4 consecutive weeks.

### Outcomes

The primary outcome of this trial is a reduction in the 11-point Numeric Pain Rating Scale (NPRS). It will be used to assess pain intensity at enrollment and at each visit. Patients will be asked to rate their weekly pain on a scale from 0 to 10 where 0 equals “no pain” and 10 equals "the worst pain they can imagine”
^27^. NPRS will be taken for both during physical activity and at rest. The difference in NRPS after first dose of esketamine and baseline will be measured to analyze efficacy.

The use of a unidimensional measure is justified as the goal of this study is to evaluate the efficacy of the investigational drug as an analgesic complement for patients already consuming morphine. There are several tools to approach pain intensity and this choice (NRPS) was based on literature review on similar situations
^27–
30^.

Oncological patients suffering from chronic pain frequently present associated degrees of depression, which is why we chose a scale evaluating exclusively pain over other multidimensional questionnaires. This strategy enables to differentiate the analgesic action of esketamine from its role as antidepressant, as this itself might improve the patients’ overall well-being and disposition.

***Secondary outcomes.***
* Sustainability of effect.* NRPS will be used to identify the pattern of effect after each dose over the 4 weeks.

*Rescue morphine use*. The use of morphine rescue (whether it will be reduced, no change, or increased). If pain decreases or stabilizes during the trial. This will be monitored using either the Aircure artificial intelligence through a mobile application or personal diaries.

*Patients’ functional status and satisfaction.* These will be measured by the change in Brief Pain Inventory (BPI). A multidimensional standardized tool as the BPI will allow the researchers to assess pain intensity in relation to its interference in functional activities
^31^.

*Depression symptoms.* Depression is frequently described in association with chronic pain and affects its threshold. On the other hand, esketamine has a proven antidepressive effect. We propose to examine a depression score using the Patient Health Questionnaire (PHQ9) at enrollment and at each visit
^32^. We would also evaluate the effect of depression on the analgesic effect of esketamine.

*Side effects.* Reported side effects in other studies include decline in mood, conscious perceptions and intellectual performance. It is well established that esketamine presents fewer side effects than the racemic ketamine
^33^. In this protocol the dissociative effects of the drug will be monitored applying the Side Effect Rating Scale for Dissociative Anesthetics (SERSDA) at enrollment and at each visit
^34^. It assesses fatigue, dizziness, headache, nausea, changes in vision and mood changes. The cognitive performance will be addressed using Speed Reading Test (where the time for reading 20 independent characters is noted)
^33^.

*Vital signs.* Blood pressure, heart rate, respiratory rate and temperature, pulse oximetry and 12-lead-ECGs will be measured at enrollment and at each visit (prior, 40 minutes and 2 hours after intranasal application of the drug or placebo). In the occurrence of any abnormality, patients will be advised to stay at the institution for complementary evaluation. Furthermore, lower urinary tract symptoms will be asked and in case of positive answers, further examination will be performed
^35^.

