## Abstract

**Background:**  Cancer is the second leading cause of death globally. Up to 86% of advanced cancer patients experience significant pain, while 10-20% live in chronic pain. Besides, increasing prescription of opioids resulted in 33,000 deaths in the US in 2015. Both reduce patients’ functional status and quality of life. While cancer survival rates are increasing, therapeutic options for chronic opioid refractory pain are still limited. Esketamine is the s-enantiomer of ketamine, with superior analgesic effect and less psychotomimetic side effects. Intranasal esketamine was approved by the FDA for treatment-resistant depression. However, its use in chronic cancer pain has never been tested. Therefore, we propose a phase II, randomized, placebo-controlled trial to evaluate the efficacy and safety of intranasal esketamine in chronic opioid refractory cancer pain.

**Methods and analysis:** We will recruit 120 subjects with chronic opioid refractory pain, defined as pain lasting more than 3 months despite optimal therapy with high dose opioids (>60 mg morphine equivalent dose/day) and optimal adjuvant therapy. Subjects will be randomized into two groups: intranasal esketamine (56mg) and placebo. Treatment will be administered twice a week for four consecutive weeks. The primary outcome is defined as reduction in the Numeric Pain Rating Scale (NPRS) after first application. Secondary outcomes include NPRS reduction after four weeks, the number of daily morphine rescue doses, functional status and satisfaction, and depression.

**Conclusion:** This study may extend therapeutic options in patients with chronic pain, thus improving their quality of life and reducing opioid use.

**Trial registration:** Clinical Trials.gov,
NCT04666623. Registered on 14 December 2020

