### Objectives

This research aims to assess the efficacy and safety of a four-week treatment with intranasal esketamine (56 mg) twice a week, combined with opioid analgesic and adjuvant standard therapy in the management of adult patients with severe and opioid refractory chronic cancer pain.
****

The primary aim is to investigate the analgesic efficacy of intranasal esketamine as an add-on therapy to potentially improve opioid resistant pain in cancer patients. We will evaluate whether intranasal esketamine alleviates chronic pain in this population by assessing the reduction with the Numeric Pain Rating Scale (NPRS) after the first dose of esketamine compared to baseline
^18^.

Our secondary aims are:

1.Assessment of safety
^19^ of this novel treatment. This will be measured by a self-reported and questionnaire-guided adverse events report.2.Evaluation if esketamine treatment reduces the number of morphine rescues required daily by the patient.3.To compare the patients’ functional status between both treatment groups.4.To evaluate the response of depression score to esketamine therapy5.To analyze if there is a difference in the efficacy of esketamine depending on the type of cancer and depression disorder of the patient.6.To analyze the sustainability of the effect after each dose throughout the time of treatment.

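### Satisfaction is listed as a secondary outcome, but its stated measure, the change in BPI, is described as covering pain intensity and interference only

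*Protocol article*

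**What the plan says.** The Abstract of the protocol article includes among the secondary outcomes "the number of daily morphine rescue doses, functional status and satisfaction, and depression". In the Secondary outcomes section, functional status and satisfaction share one heading, and the measure given for the pair is "These will be measured by the change in Brief Pain Inventory (BPI". The sentence that follows explains the choice: "A multidimensional standardized tool as the BPI" "will allow the researchers to assess pain intensity in relation to its interference in functional activities".

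The Objectives section lists six secondary aims. The third reads "To compare the patients’ functional status between both treatment groups". Satisfaction is in none of the six.

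Functional status has one further mention, under Blinding, as part of the weekly evaluation: "Also a physical examination will take place to follow up the patients’ functional status".

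**The concern.** The plan names two constructs and gives both the same change score. Its own account of the instrument fits one of them, since interference with activities is a reasonable reading of functional status. It does not fit the other. How much pain a patient has, and how far it limits activities, is a different question from whether the patient is satisfied with the treatment.

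What is at stake is a conclusion. If the BPI improves more on esketamine, the plan as worded licenses a statement that satisfaction improved. If the BPI does not move, it licenses the opposite statement. In neither case would the described measurement support a claim about satisfaction.

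A later analysis plan cannot repair this fully. It can choose which score to take from data already collected, but it cannot supply answers to a question that patients were never asked. The matter therefore has to be settled before enrolment.

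**Working it through.** No figure in the plan bears on this point, so there is nothing to recompute. The sample size (108, raised to 120 for dropout) is built on the NPRS and does not involve the BPI. The check is a comparison of the places where the two constructs appear.

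1. **Where satisfaction is named.** Two places: the Abstract and the Secondary outcomes section. In both it is joined to functional status.
2. **What measures it.** Only the change in BPI, under Secondary outcomes. The plural subject of that sentence takes in both constructs, so satisfaction is given a measure rather than left open.
3. **What that measure is said to capture.** By the protocol's description, the BPI serves to "assess pain intensity in relation to its interference in functional activities". That covers two contents, intensity and interference. Satisfaction is neither.
4. **Whether another instrument fills the gap.** The other instruments named are:
   - the NPRS, for pain intensity;
   - the PHQ9, for depression;
   - the SERSDA, for side effects;
   - the Speed Reading Test, for cognitive performance;
   - a mobile application or diary, for rescue morphine.

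   None is assigned to satisfaction.
5. **Whether an aim depends on it.** The six secondary aims are safety, number of morphine rescues, functional status, depression score, differences in efficacy by cancer type and depression, and sustainability of effect. None is satisfaction.
6. **The same test for functional status.** It has an aim (the third), a measure (the BPI), and a description of that measure which refers to functional activities. The weekly physical examination under Blinding adds a second source, though it has no score and is not designated as the outcome measure. Functional status passes the test that satisfaction fails.

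The outcome lists therefore promise something that the aims do not call for and that the assigned tool, as described, does not capture.

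**The case against.** The strongest reply is that the plan does assign a measure, and that a one-sentence description of a multidimensional tool is not a list of its items. The version to be used might contain an item that the sponsor intends as satisfaction. This stands as a limit on the claim. A reader might infer that the BPI holds no satisfaction item, or that satisfaction is not measured at all. The documents do not support that, because they show neither the questionnaire nor the case report form. What can be said is that the protocol's own description does not mention satisfaction. If a particular item is meant, the protocol should name it.

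A second reply is that an article leaves such detail to the full protocol or analysis plan. That would answer a complaint about an unstated detail. Here, however, the article states a measure, and the measure does not match its construct.

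A reader might also go further and infer that the functional outcome merely repeats the pain outcome, since the BPI includes intensity and the primary outcome is intensity on the NPRS. The documents do not support this either. It would require a pooled BPI total, or the intensity items, to be scored as function, and no section says so. The Secondary outcomes section ties function to interference, and the choice of BPI score is the kind of detail commonly left to the full protocol or analysis plan. Any figure for the amount of pain carried into the functional score would rest on a weighting that the plan does not give.

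Finally, no stated aim depends on satisfaction. That is correct. It limits the consequence, and it makes removing the term an acceptable remedy.

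**Conclusion.** The point holds for satisfaction and is minor. One named secondary outcome is assigned a measure whose described content does not include it, and the Abstract and Secondary outcomes do not match the Objectives. As written, a BPI change would be reported as a satisfaction effect. The primary outcome, its sample size, the safety assessments and the functional outcome are unaffected.

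The conclusion rests on one assumption: that the protocol's description of the BPI is a fair account of what it is meant to contribute. If the sponsor can point to a BPI item that it intends as satisfaction, the remaining defect is only that this item is not identified.

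**What to change.** Choose one of two changes before recruitment starts.

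- **Keep the outcome.** Add one patient-rated item on satisfaction with treatment at the existing week 4 visit, name it under Secondary outcomes as the satisfaction measure, and compare it between the arms. The cost is one extra question for each patient. Satisfaction is already on the outcome list, so this does not lengthen the list.
- **Drop the outcome.** Remove satisfaction from the Abstract and from the Secondary outcomes heading, so that both match the Objectives. The cost is a change of wording, and the trial then makes no statement about satisfaction.

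In the same edit it would help to state that functional status is the change in BPI interference. This fits the rationale already given under Secondary outcomes and costs nothing. It is a clarification, not the correction of a demonstrated error.
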